## Abstract

**Introduction:**

People with kidney failure receiving haemodialysis experience significantly high rates of depression. However, there is a lack of evidence on how to treat depression in this population. A significant barrier to effective treatment is the high treatment burden of haemodialysis, which makes additional appointments prohibitive. Behavioural activation (BA) is an evidence-based brief therapy for depression that has been delivered in a variety of different clinical settings. However, it has not previously been evaluated in the haemodialysis setting.

**Methods:**

This study aims to evaluate the feasibility and acceptability of a cluster randomised controlled trial (cRCT) of intradialytic BA for people with kidney failure. The study consists of three main components: A pilot cRCT, where we will recruit 52 people who are receiving haemodialysis and experiencing symptoms of depression across two sites. Patients will be cluster-randomised to either BA or usual care and will be followed up for three months; a qualitative process evaluation using semi-structured interviews to explore the experiences of patients, healthcare professionals and carers; and a feasibility economic evaluation exploring the feasibility of collecting healthcare resource use data.

**Results:**

Key findings will include the feasibility of screening and recruiting participants, participant retention, completion of clinical outcome measures, and the acceptability of the intervention.

**Conclusion:**

If feasible, the next step will be to conduct a definitive, adequately powered cRCT to determine the effectiveness of the intervention in this population, so that we can improve the identification and management of depression for people with kidney failure.

## Introduction

Depression has serious implications for the overall health of people receiving haemodialysis [1–3]. Depression is associated with decreased quality of life and increased morbidity [4] and is an independent predictor of mortality, in part due to the impact that depression has on adherence to treatment [4]. People experiencing depression are less likely to be adherent to their treatment regimen [4], increasing their risk of hospitalisation, morbidity and death [5]. Therefore, the issue of depression must be addressed amongst people receiving haemodialysis, to improve long-term outcomes for these patients, their families and carers and reduce the economic burden on the health service.

Improving mental health support for people receiving haemodialysis has been identified as a priority by Kidney Care UK’s Psychosocial Health – A Manifesto for Action [6]. Currently, there is limited evidence on the effectiveness of antidepressant medication amongst people receiving haemodialysis [7], in part because of the difficulties in trial design and the adverse events associated with medication [3,7–9].

Cognitive behavioural therapy (CBT), another evidence-based treatment for depression, appears to be more effective at reducing symptoms of depression among people with kidney disease [10,11]. However, issues surrounding long-term implementation in practice, such as the need for a trained clinical psychologist to deliver the intervention [11], the requirement to attend separate appointments (either in-person, online, or over the phone) [12,13], raise concerns about feasibility when resources are significantly limited, and patients already face a substantial treatment burden [7,8].

Behavioural activation (BA) is an evidence-based psychological therapy that forms a key part of CBT. BA is based on making small changes in daily life to disrupt negative cycles of thoughts, feelings, and behaviour [13]. While there is evidence that CBT can improve depression among people with chronic kidney disease (CKD), treatment burden limits the accessibility of CBT and there is a lack of evidence supporting the effectiveness of BA alone [10]; however, it has been shown to be effective in the treatment and prevention of depression in the general population [14,15], and can be more cost-effective than traditional CBT [16]. Consequently, BA is recommended by the National Institute for Health and Care Excellence (NICE) guidelines on the management and recognition of depression in adults with chronic physical health problems [17].

There is a growing recognition of the need to integrate mental and physical health services, particularly to benefit people who have long-term physical health conditions, such as kidney failure [3,18–20]. This integration is of particular importance for people receiving haemodialysis, due to the impact of the treatment on mental health [21,22]. A specific benefit of BA for this population is that it can be delivered outside of mental health services and has been successfully integrated into other services, such as primary care, where it has been delivered by trained non-specialists [23–25]. However, while there is a need to establish the effectiveness of BA for reducing symptoms of depression among people receiving haemodialysis, the feasibility of integrated BA in haemodialysis settings is unknown [10]. Therefore, a feasibility study is needed to determine whether the integrated delivery of BA is possible and acceptable before any assessment of effectiveness [26–29].

### Aims and objectives

This study aims to establish the feasibility and acceptability of a behavioural activation intervention, integrated into haemodialysis care, to address symptoms of depression and anxiety amongst people with kidney failure who are receiving maintenance haemodialysis. To achieve this, we will meet the following objectives:

Determine the feasibility of recruiting, randomising, and retaining participants, including screening for depression using the PHQ-4, in a definitive cRCT.Evaluate the feasibility of data collection methods within a cRCT.Evaluate the feasibility of conducting a future economic evaluation of an integrated behavioural activation intervention.Explore the acceptability of the integrated behavioural activation intervention for patients, healthcare professionals and informal carers.Refine the process for evaluating intervention fidelity in a definitive cRCT.

## Materials and methods

### Study design

This study comprises a comprehensive mixed-methods feasibility study with three main components: a feasibility cluster randomised controlled trial (cRCT), a feasibility economic evaluation, and a process evaluation. This protocol is reported in accordance with the SPIRIT checklist for trial protocols [30]. This study has been prospectively registered on ISRCTN (ISRCTN74685186) [28], and received ethical approval from the London – Dulwich Research Ethics Committee (REC Reference: 25/LO/0920).

### Research setting

This study will take place in two haemodialysis units in England, one in Hull and one in London. Recruiting from two different geographic areas with varying levels of deprivation will enable us to explore different clinical and socioeconomic factors that may influence recruitment and participation in a definitive trial. Recruitment and data collection will take place in the summer and autumn of 2026.

### Feasibility cRCT

#### Study population.

**Inclusion criteria.** Patients will be eligible for participation if they:

Are over 18 years of age.Are receiving maintenance in centre haemodialysis for > 3 months and will continue to receive haemodialysis in the unit for the duration of the study.Have the capacity to provide informed consent.Score ≥ 3 on the screening PHQ-4

Depression is not regularly screened for within practice, despite recommendations from recent reports on depression in people with kidney disease [6]. There is also evidence that people receiving haemodialysis are reluctant to undergo screening for depression [29]. Therefore, we will be unable to screen using routinely collected data. Instead, we will screen all potentially eligible patients at each unit using the PHQ-4. This is a valid ultra-brief tool that can detect both anxiety and depression. Patients who score three or higher on the PHQ-4 will be invited to participate in the study [31]. All patients who screen positive using this threshold will be provided with information on support services

**Exclusion criteria.** Patients will be ineligible for participation if they:

Started antidepressant medication or forms of talking therapy within the previous three months.Are receiving haemodialysis for acute kidney injuryHave a planned kidney transplant within the study periodAre planning to move from the dialysis unit during the study period, either because they are moving home to a different catchment area, are planning to move to a satellite dialysis unit, or are planning to start home haemodialysisDo not have the capacity to provide informed consent. The clinical judgement of the dialysis team will determine the capacity to consent. We will develop recruitment materials for participants who may require additional communication support, in line with ASSENT guidance, to ensure we are not unfairly excluding eligible patients.Are unable to understand and communicate effectively in English.

#### Sample size.

As this is a feasibility study, a power calculation was not conducted, as we are not looking to measure effectiveness. There is no consensus on the appropriate sample size for a feasibility study [32,33]. However, a total sample size of 52 people would allow us to estimate the recruitment rate with a precision of ±9% (assuming a previously observed 40% recruitment rate and a 95% confidence interval). This provides an appropriate level of precision to inform the likely number of people the full-scale trial might need to screen. Given that we have four clusters, this would also allow for a minimum of 12 participants per cluster, with a total of 26 participants recruited from each site [34].

#### Recruitment.

Following the initial screen, participants will be approached by the researcher, who will explain the study, provide the participant information sheet, and answer any questions they may have. At the next scheduled haemodialysis appointment, the researcher will approach the patient again and obtain informed consent if they are interested in participating. Screening logs will be used to capture the proportion of patients who are eligible for screening, the proportion of people who are eligible following screening, and the proportion of participants who consent and are randomised.

#### Randomisation.

Following the collection of baseline data from all enrolled participants, patients will be grouped into clusters based on their dialysis shift patterns. These shift patterns will be randomly assigned using Stata19 [35] to either the control group, where enrolled participants will receive enhanced usual care, or the intervention group, where enrolled participants will receive the intervention. We will explore the feasibility of cluster randomisation according to the dialysis shift pattern.

Cluster randomisation by dialysis shift pattern will be used to prevent inter-arm contamination, as the intervention is delivered bedside. We will monitor shift changes and potential contamination (e.g., control participants observing intervention delivery) to assess the feasibility of this randomisation strategy. The cluster pattern is shown in Fig 1.

**Fig 1 pone.0353407.g001:**
[figure not shown]
Proposed dialysis shift clusters at each site for randomisation.

#### Intervention.

A BA workbook was adapted from the ComBAT intervention [36] and other BA interventions specifically designed for individuals with long-term conditions. This workbook was then shared with our PPI panel for further adaptation to the haemodialysis setting. Each participant allocated to the intervention group will receive at least 6 one-to-one sessions, delivered at their bedside during their haemodialysis treatment. Participants will receive a BA workbook to support the content of each one-to-one session and to refer to between sessions. At the end of each session, the facilitator and participant will plan take-away activities to do outside of the sessions. Fig 2. Provides an overview of the BEACH intervention.

**Fig 2 pone.0353407.g002:**
[figure not shown]
Overview of the BEACH intervention.

Using a standardised training programme, we will train kidney health professionals to deliver the BA intervention as facilitators. The training will involve one face-to-face workshop that includes both a theoretical component explaining what BA is and how it works and a skills-based component featuring case scenarios and role-plays. While the content will be organised into 5 key modules, the pacing of session content will be tailored to the participants’ needs. Following the training, the BA facilitators will be offered supervision as needed, both individually and in groups, at most once a week for 30 minutes and at least once a month for 1 hour.

#### Intervention fidelity.

Intervention fidelity will be evaluated using session logs. The BA facilitators will be asked to complete a session log following each session, which will record the session length and include a menu of intervention components (e.g., that could be delivered during the session. These will be reviewed to identify whether core aspects of BA have been delivered as intended.

At follow-up, all participants will be invited to complete the Aspects of Care Questionnaire to help assess fidelity and contamination. The questionnaire has eight items that correspond to general activities that may have taken place within both randomisation arms (e.g., “I had an opportunity to talk about my current problems/general life”) as well as BA-specific activities (e.g., “I wrote down things I did for pleasure and necessary tasks on a weekly calendar”). We will compare responses between BA and control group participants to determine whether BA participants received the core components of the intervention as intended (fidelity) and whether control participants inadvertently received BA components (contamination) [36].

#### Usual Care.

There is no standardised usual care for depression provided within haemodialysis units across the UK, and few units implement NICE guidelines for the assessment and management of depression in long-term conditions. Usual care typically takes the form of internal or external signposting to services, within the NHS or primary care, or through third-sector providers such as Kidney Care UK [6]. Therefore, the control group participants will be provided with information on available services and sign-posted to the relevant service.

#### Data collection.

Baseline demographic and clinical data. We will collect data on participants’ age, sex, ethnicity, employment status, Index of Multiple Deprivation, time on dialysis, primary kidney diagnosis, and comorbidities. We will also collect self-reported data on whether participants have received a diagnosis of depression at any time in their life, if they are receiving any treatment for mental health conditions, and what that treatment entails.

Feasibility measures. The main outcome of the pilot cRCT is feasibility, which will be evaluated by collecting descriptive data on recruitment, retention, and participants’ willingness to be randomised, in accordance with the CONSORT guidelines for feasibility and pilot trials [37]. The following data will be collected:

**Willingness to screen:** The proportion of individuals who agree to undergo the initial screening for depression with the PHQ-4.**Eligibility Criteria Suitability:** The number of individuals excluded from the trial and the specific reasons for exclusion will be recorded to assess the appropriateness and practicality of the inclusion and exclusion criteria.**Willingness to Participate/ Recruitment rate:** The proportion of eligible individuals who consent to participate in the trial will be recorded as a measure of feasibility and acceptability.**Retention Rates:** The proportion of randomised participants who remain in the study and complete the follow-up assessments will be documented. Follow-up contact will be made, where possible, to ascertain the reasons for discontinuation in cases of participant drop-out.**Intervention adherence:** The proportion of participants allocated to the intervention group who complete the intervention, as well as the proportion of missed and incomplete sessions, will be recorded in session logs.**Time required for data collection and analysis:** Time for screening, consent, and follow-up will be recorded via timesheets to inform timelines and milestones in a future trial.**Feasibility of outcome measures**: The proportion of missing data from each of the outcome measures will be reported to determine the feasibility of collecting complete data using the identified outcome measures.

These measures of feasibility and acceptability will also be explored in more detail in the qualitative process evaluation.

Clinical outcome measures. Most studies evaluating BA have a follow-up period of less than 3 months [15]; therefore, we will administer the clinical outcome measures at baseline and at 3 months post-randomisation. The clinical outcomes will include depression, as measured by the PHQ-9, a commonly used measure of depression that has been psychometrically validated within people who have kidney failure [38]. We will also capture anxiety, measured using the GAD-7 [39], health-related quality of life, measured by the KDQOL-SF36 [40], mental well-being, measured by the WEMWBS [37], and adherence to haemodialysis, measured by dialysis attendance captured in the healthcare resource use logs, and completion of full-length sessions. An overview of the schedule of clinical outcome measures is shown in the SPIRIT Figure in Fig 3 [30].

**Fig 3 pone.0353407.g003:**
[figure not shown]
Participant timeline: Schedule of enrolment, interventions, and assessments.

#### Data analysis.

To address the primary feasibility outcomes, a variety of approaches will be used. Descriptive statistics will be used to present baseline demographic and clinical data. Categorical data will be presented as frequencies, and continuous data as means. Summary statistics will be used to describe the proportions of patients approached who consent to screening, are eligible, consent to the study, are randomised, and are retained and followed up. The proportion of people who complete the intervention, the number of intervention sessions received, and the number of adverse events will be summarised. For continuous secondary outcome variables measured at 3-months, effects sizes with 95% CIs will be estimated using linear regression models, with group allocation and the baseline value of the outcome included as covariates.

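### The outcome regression omits the randomised unit (four shift clusters), so its 95% CIs are too narrow if outcomes correlate within shift

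*Protocol article*

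**What the plan says.** All references are to the protocol article, Feasibility cRCT part.

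- **Randomisation:** the unit is the shift pattern, not the patient: "These shift patterns will be randomly assigned using Stata19 [35] to either the control group" or the intervention group. The reason given is "Cluster randomisation by dialysis shift pattern will be used to prevent inter-arm contamination, as the intervention is delivered bedside".
- **Sample size:** "Given that we have four clusters, this would also allow for a minimum of 12 participants per cluster". The same section plans equal recruitment at the two sites, 26 patients each. With 52 patients the mean cluster size is 52/4 = 13.
- **Data analysis:** for continuous secondary outcomes at 3 months, "effects sizes with 95% CIs will be estimated using linear regression models, with group allocation and the baseline value of the outcome" as the covariates.

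The article mentions no cluster term, random effect, cluster-level analysis, cluster-robust or small-sample-corrected standard error, ICC or design effect.

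**The concern.** Patients who dialyse on the same shift share staff, facilitators, timetable and unit. They are also allocated together. If their outcomes are correlated after baseline adjustment, a difference between arms carries variation between shifts as well as variation between patients. Ordinary regression on patients counts only the second. It also uses residual degrees of freedom close to the number of patients, although only four units were randomised.

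At stake are the between-arm intervals for PHQ-9, GAD-7 and the other continuous secondary outcomes. A nominal 95% interval would suggest more precision than four clusters can give. The study also exists to try out the methods of a definitive cluster trial, and an analysis that leaves out the cluster does not rehearse that trial's analysis.

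**Working it through.** **Inputs from the article.** Four clusters, 52 patients (13 per cluster), two sites of 26, and a model containing arm and baseline value.

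**Assumptions.**
- ICC of the baseline-adjusted outcome: none is given, so 0 to 0.10 is shown.
- Patients analysed per cluster: 13 (everyone), or 10 (about 80% followed up, 0.8 × 13 = 10.4).
- Two clusters per arm. For the site calculation in step 5, one cluster per arm at each site. The Randomisation text states neither, and Fig 1 is not shown.

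**1. The plan's own figure.** The Sample size section says "a total sample size of 52 people would allow us to estimate the recruitment rate with a precision of ±9" per cent, at a 40% recruitment rate. 52/0.40 = 130 people approached. The Wald half-width is 1.96 × √(0.4 × 0.6/130) = 8.4 points. The exact interval for 52/130 is 31.5% to 49.0%, that is −8.5/+9.0 points. The figure is reproduced and is not affected by this point.

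**2. Degrees of freedom.** Patient-level regression with everyone analysed has 52 − 3 = 49 df, t = 2.01. With 40 analysed it has 37 df, t = 2.03. Four clusters less two arms leave 2 df, t = 4.30.

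**3. Design effect and coverage.** The design effect is DE = 1 + (m − 1) × ICC. The true standard error is about √DE times the one reported. Coverage is simulated with at least 20,000 trials per ICC.

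| ICC | DE, m = 10 | √DE | Coverage, m = 10 | DE, m = 13 | √DE | Coverage, m = 13 |
|---|---|---|---|---|---|---|
| 0 | 1.00 | 1.00 | 95% | 1.00 | 1.00 | 94.9% |
| 0.01 | 1.09 | 1.04 | 93.9% | 1.12 | 1.06 | 93.3% |
| 0.02 | 1.18 | 1.09 | 92.7% | 1.24 | 1.11 | 92.1% |
| 0.05 | 1.45 | 1.20 | 89.5% | 1.60 | 1.26 | 87.5% |
| 0.10 | 1.90 | 1.38 | 84.5% | 2.20 | 1.48 | 80.4% |

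Analytic check at m = 10, ICC 0.05: 2Φ(1.96/√1.45) − 1 = 0.896, in line with the simulated 89.5%. A cluster-mean comparison without site, on 2 df, held about 95% coverage throughout.

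**4. Width of a valid interval** (m = 10, ICC 0.05, outcome residual SD = 1).
- Cluster level: with two clusters per arm, the SE of the difference is √(0.05 + 0.95/10) = 0.381. The mean of an SD estimated on 2 df is √π/2 = 0.886 of its true value. Mean half-width: 4.30 × 0.381 × 0.886 = 1.45 SD.
- Planned model: about 2.03 × 2/√40 = 0.64 before a small reduction because the residual SD is slightly underestimated; the simulated mean is 0.63 SD.
- Ratio: 1.45/0.63 = 2.3.

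**5. Adding site.** Each shift belongs to one site, so adjusting for site uses one between-cluster df: 4 − 2 − 1 = 1, with t = 12.7. Let d₁ and d₂ be the arm differences at the two sites. The estimate is (d₁ + d₂)/2 and its correct SE is |d₁ − d₂|/2. After residualising on site, the two-sample formula on four means gives |d₁ − d₂|/(2√2), so the statistic is √2 times a Cauchy variable. A t(2) interval then covers (2/π) × arctan(4.303/√2) = 0.80, at any ICC. With t(1), coverage returns to 95%. If both shifts at a site fell in the same arm, adjusting for site would remove the arm contrast altogether.

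**The case against.** **These estimates decide nothing.** The Sample size section disclaims measuring effectiveness, feasibility is the main outcome, and the Progression criteria rest on recruitment, contamination, acceptability and missing data. This stands, and it limits the severity. It does not make a nominal 95% interval valid; if the estimate is not wanted, the interval can be left out.

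**A condensed article may leave the variance estimator to an analysis plan.** Cluster-robust or corrected errors are not excluded. This stands in part. But the article names the model, both covariates and the interval, so this is a stated specification and not simply an omitted detail. The usual unstated additions, an uncorrected sandwich error or mixed model, are also unreliable with four clusters.

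**The ICC could be near zero.** This stands. At 0.01 to 0.02, coverage is still 92-94%.

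**Stronger inferences that the article does not support.**
- A reader might infer that these intervals are the trial's only inferential output. The Sample size section also plans a recruitment rate with 95% confidence precision.
- A reader might infer that the effect sizes will set the size of the definitive trial. No section says so.

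**Conclusion.** The stated model leaves out the unit of randomisation, and that follows directly from the text. That the intervals are too narrow is conditional on a positive baseline-adjusted within-shift ICC; it would be going too far to say that they are certainly too narrow. Under two clusters per arm and 10 to 13 analysed per cluster, the loss of coverage ranges from negligible near ICC 0 to roughly 10 to 15 points at ICC 0.10. Because the outcomes are secondary and have no role in progression, this is a should-fix and not a defect that undermines the study.

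**What to change.** Replace the regression sentence in the Data analysis section with one of the following.

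- **(a) Descriptive.** Report means and SDs at baseline and 3 months by arm and by shift cluster, with the baseline-adjusted difference and no between-arm interval. This is the simplest option and fits the statement that effectiveness is not being measured.
- **(b) Cluster level.** Regress the 3-month outcome on its baseline value only, without arm or site. Average the residuals by shift cluster, and compare arms on the four means with a t interval on 2 df. State that the intervals will be very wide.

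If site is also adjusted for and each site has one shift per arm, use t on 1 df. Do not rely on an uncorrected mixed model or sandwich standard error with four clusters.

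The cost is one sentence and no extra data. Under (a) the intervals are lost. Under (b) they become much wider, by the factor worked out in step 4 if the ICC is 0.05.

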## Discussion

People with kidney failure receiving haemodialysis are at higher risk of developing mental health conditions, such as depression [3]; despite this, there is currently limited access to support and specialist mental health services. Alongside current barriers to accessing support, such as long waiting times, patients spend a significant portion of their week attending dialysis appointments [6,7]. One potential solution is to explore ways to improve access to mental health support and treatment within their existing treatment regimen.

While BA is a NICE-recommended treatment for depression in adults, including those with co-occurring long-term conditions [17], it has never been delivered or evaluated for patients with kidney failure during their routine haemodialysis appointments [10,49]. Therefore, our primary aim isn’t to explore its effectiveness, but rather to first assess the feasibility and acceptability of delivering BA during haemodialysis. We will explore this through various methods; firstly, a pilot cRCT to determine the feasibility of conducting a definitive cRCT to evaluate the BA intervention, secondly, a qualitative process evaluation to explore the acceptability of the intervention and methods, and finally, a feasibility economic evaluation to explore the best methods for evaluating cost-utility in a definitive trial.

A key strength of this study is that the intervention was adapted in close collaboration with patients and carers, with the aim of further refinement following delivery within the pilot cRCT. The protocol follows the Medical Research Council’s (MRC) guidance on the evaluation of complex interventions [27], using a comprehensive mixed-methods approach to explore feasibility and acceptability. While the study will involve only two sites in England and we do not have the resources to translate and culturally adapt the intervention, which limits the generalisability of the findings, we have deliberately selected sites that serve different demographics. Therefore, the feasibility study will provide us with an understanding to refine the protocol and intervention for a future definitive cRCT.

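### The 3-month outcome regressions omit site, although the two sites were chosen to differ; at planned shift sizes the effect is small, and a site term is a cheap safeguard

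*Protocol article*

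**What the plan says.** The Data analysis section of the feasibility cRCT fixes the model: "For continuous secondary outcome variables measured at 3-months, effects sizes with 95% CIs will be estimated" by "linear regression models, with group allocation and the baseline value of the outcome included as covariates". No other covariate is named.

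Site is nevertheless part of the design. Under Research setting: "This study will take place in two haemodialysis units in England, one in Hull and one in London", with the reason that "Recruiting from two different geographic areas with varying levels of deprivation will enable us to explore different clinical and socioeconomic factors". The Discussion repeats this: "we have deliberately selected sites that serve different demographics".

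Under Sample size: "Given that we have four clusters, this would also allow for a minimum of 12 participants per cluster, with a total of 26 participants recruited", the last figure being per site. The caption of Fig 1 places the shift clusters within each site. The Randomisation section assigns shift patterns at random and states no restriction or stratification by site.

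**The concern.** Site is known for every participant before randomisation, and the authors expect the sites to differ in ways that may matter for outcome. With only four clusters, the mix of sites need not be the same in the two arms. Where it is not, a model without site attributes part of the site difference to BA. Where it is the same, site variation stays in the residual and the model-based interval is slightly wider than it need be.

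At stake are the secondary effect estimates and their confidence intervals. The feasibility outcomes and the progression criteria do not depend on this model. The lack of any term for dependence within shifts is a separate matter that a site term does not settle.

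**Working it through.** **The plan's own figures.** The protocol gives no site difference, SD or intracluster correlation. Its one computed figure, ±9% for the recruitment rate, plays no part here. It does reproduce: 52/0.40 = 130 people approached, and 1.96 × √(0.4 × 0.6/130) = 8.4% (exact interval −8.5/+9.0 points). The relevant figures are four clusters, at least 12 in each, and 26 per site. With two shifts per site, that means shifts of 12 to 14.

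**Formula.** Let Δ be the site difference at 3 months that remains after baseline adjustment. Without a site term, the BA coefficient absorbs

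leak × Δ, where leak = (site A's share of the BA arm) − (site A's share of the control arm).

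**Leak by shift size** (BA/control at site A; BA/control at site B), with an assumed Δ of 2 PHQ-9 points:

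| Shift sizes | Leak | Shift in estimate |
|---|---|---|
| 13/13; 13/13 | 0 | 0 |
| 14/12; 14/12 | 14/28 − 12/24 = 0 | 0 |
| 14/12; 12/14 (worst case as planned) | 14/26 − 12/26 = 0.077 | 0.15 |
| 16/10; 13/13 | 16/29 − 10/23 = 0.117 | 0.23 |
| 16/10; 10/16 | 16/26 − 10/26 = 0.231 | 0.46 |
| 18/8; 8/18 | 18/26 − 8/26 = 0.385 | 0.77 |

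The BA:control ratio has to differ between the sites. Unequal shifts with the same ratio at both sites give no leak.

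**Range for Δ.** For Δ of 0.3, 0.5 and 1.0 SD, the shift is 0.02, 0.04 and 0.08 SD at the planned worst case; 0.07, 0.12 and 0.23 SD at 16/10 and 10/16; and 0.12, 0.19 and 0.38 SD at 18/8 and 8/18. The standard error is about 0.24 SD.

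**Coverage.** Simulation used 3000 runs, baseline correlation 0.5, no shift effect and no true BA effect. Without site, 95% intervals covered 95 to 97% at the planned worst case, and 93%, 88% and 75% at 18/8 and 8/18 for the three values of Δ. With site in the model, bias was about 0 and coverage 94 to 95% in these settings.

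**Standard error in PHQ-9 points** (assumed SD 5, correlation 0.5, Δ = 2). The residual variance is 25 × (1 − 0.25) = 18.75.
- Equal shifts with site: √(18.75 × 2/26) = 1.20.
- Equal shifts without site: Δ²/4 = 1 is added, so √(19.75 × 2/26) = 1.23 (simulated 1.24).
- 18/8 and 8/18 with site: √(18.75/(2 × 18 × 8/26)) = 1.30 (simulated 1.31), against 1.23 without.

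**Allocation.** Take shifts of 16 and 10 at each site, with one BA shift per site. The four possible allocations give leaks of +0.23, 0, 0 and −0.23, which average zero. If instead any two of the four shifts may be drawn for BA, 2 of the 6 allocations put a whole site in each arm. The leak is then 100%, and a site term cannot be estimated.

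**The case against.** The strongest reply is that the size is trivial under the plan. At 12 to 14 per shift, at most 0.15 points leaks against a standard error near 1.24, in secondary estimates from a study that says it does not measure effectiveness. That stands. It depends on shift sizes that are expected rather than enforced: no quota per shift is stated, patients are grouped by shift only after enrolment, and dropout changes the analysed numbers again.

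Baseline adjustment also removes part of a site difference. If the sites differ by 2 points at both baseline and 3 months, a correlation of 0.5 with equal SDs leaves 2 − 0.5 × 2 = 1 point and halves the figures in points above. That stands too.

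Three stronger readings are tempting, and the document does not support them.
- A reader might infer that unequal shifts systematically bias the BA effect. They do not: the ratios must differ between sites, and the error averages zero over allocations.
- A reader might infer from "There is no standardised usual care for depression provided within haemodialysis units across the UK" that the two sites' controls receive different care. The same section goes on to one package for all controls: "the control group participants will be provided with information on available services and sign-posted to the relevant service". Differences in usual care or facilitators would in any case act mainly as a BA effect that varies by site, which a site main effect does not remove.
- A reader might infer that these estimates decide the definitive trial. The Progression criteria rest on recruitment, contamination, acceptability and missing data.

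**Conclusion.** The point holds as a minor improvement to a model that the protocol spells out. Omitting site lets at most 7.7% of the baseline-adjusted site difference into the BA estimate at planned sizes, which is negligible beside sampling error. The share reaches 23% to 38% only if recruitment or dropout produces markedly unequal shifts running in opposite directions at the two sites. With arms balanced within site, the only consequence is a slightly wide interval (standard error 1.24 rather than 1.20).

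These sizes rest on two shifts per site and one BA shift at each. The figures in points also assume a 2-point site difference, SD 5 and baseline correlation 0.5, none of which the protocol gives. The larger exposure is structural: the Randomisation text does not say that each site has both arms. Fig 1, which could not be seen for this review, may settle that.

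**What to change.** In the Data analysis section, add a site indicator to each patient-level regression: outcome at 3 months on allocation, baseline value and site. In the Randomisation section, confirm that allocation is restricted so that each site has one BA and one control shift. Without that restriction the term may be inestimable. Settling both before recruitment avoids choosing covariates after seeing the data.

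The cost is one residual degree of freedom and some precision if shifts are very unequal (standard error 1.31 rather than 1.23 at 18/8 and 8/18). The advice applies to the patient-level model as stated. In a cluster-level analysis of four clusters, a site term would cut the degrees of freedom from 2 to 1 and raise the 95% critical value from 4.30 to 12.7, so it should not be carried over automatically.
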